## 9.2. Exclusion criteria

1. Other causes except for cardiogenic shock (low blood pressure, septic, obstructive shock)
2. Shock with cardiac arrest outside the hospital
3. People with allergic reactions to anticoagulants such as heparin
4. Those who refused active treatment

## 9.3. Targeted sample size and their basis

- (1) Estimated enrollment: 1000 participants (competitive registration after registering 1,000 participants)

- The group with left ventricular assist device insertion: more than 400 participants
- The group without left ventricular assist device insertion: more than 600 participants

### (2) Background

Samsung Medical Center, Korea University Anam Hospital, Sejong General Hospital, Bucheon, Samsung Changwon Hospital, Ilsan Paik Hospital, Dankook University Medical Center, Konkuk University Medical Center, Chung-Ang University Hospital, Inha University Hospital, and Chungbuk National University Hospital are expected to participate, and considering the fact that 1,800 patients with acute myocardial infarction are being treated annually in 10 hospitals, about 5.5% of myocardial infarction patients progress to shock, which means that about 100 patients can be registered each year, and it is estimated that more than 100 patients can be registered due to other causes such as unstable angina, shock during procedures, cardiomyopathy, and myocarditis. Considering the five-year study period, it is estimated that more than 1,000 patients can be registered.

As for the group with left ventricular assist devices (LVADs) inserted, most of them are critically ill patients, so it should be noted that a comparison with the group without LVADs inserted cannot be made on an equal footing. However, other than that, sample size/power calculations for binomial proportions were applied using Fleiss, Tytun, and Ury (1980). With the above number of patients, it has about 88% statistical power to detect an odds ratio of 1.56 (inserted group = 0.3, non-inserted group = 0.4). However, if an expected dropout rate of about 10% is taken into account, the power is reduced to 84%.

In addition, considering that the group with LVADs inserted is significantly superior to the group without LVADs, a one-sided test is usually performed, and when adjusted, the power exceeds 90%. Therefore, it is expected that this clinical trial plan will be statistically and clinically successful when executed.

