## **9. Inclusion criteria, exclusion criteria, and targeted sample size and their basis**

### **9.1. Inclusion criteria**

1. 19 years old or older
- 2-1). Systolic blood pressure is less than 90mmHg for more than 30 minutes despite the fluid therapy, or Use of pressure boosting agents is necessary.
- 2-2). Peripheral hypoxia (cold skin, urine less than 30 cc per hour, impaired consciousness, lactate  $\geq 2.0$  mmol / l) or a person with pulmonary edema.
3. Causes of cardiogenic shock include acute myocardial infarction (including in coronary intervention), cardiomyopathy, myocarditis, pulmonary embolism, refractory ventricular tachycardia, shock during coronary intervention.
4. In-hospital cardiac arrest as a result of the cause stated in 'inclusion criteria 3'.
5. Those voluntarily consenting to the medical records and the data necessary for the study during the entire study period.

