### **15.3. Statistical analysis**

We aim to identify predictors of in-hospital death in patients who experience shock using binary logistic regression analysis. This type of analysis requires 10-15 events per independent variable, and with an expected mortality rate of about 40%, or approximately 400 deaths, we have sufficient events to study various risk factors. The goodness-of-fit of the model will be assessed using the C-statistic and Hosmer-Lemeshow test. In addition, we plan to compare the in-hospital death rate between patients with and without left ventricular assist devices using chi-square tests among those who receive a certain level of vasoactive drugs. We also aim to identify predictors of successful removal of the ECMO device and procedure-related complications such as bleeding, thrombosis, and limb ischemia using binary logistic regression analysis in patients who undergo ECMO. Finally, we plan to evaluate overall death over five years using Cox survival

analysis. We will assess the goodness-of-fit of the model by checking Schoenfeld's residuals and identify the hazard of each risk factor.

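### The 88% / 84% / over-90% power in section 9.3 is for all 400 vs 600 patients, but section 15.3 tests the device effect only in a vasoactive-drug subset of unstated size; the planning rates also imply about 360 deaths, not 400

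*Protocol*

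**What the plan says.** **Sample size.** Protocol section 9.3 (1) sets "Estimated enrollment: 1000 participants (competitive registration after registering 1,000 participants", split as "The group with left ventricular assist device insertion: more than 400 participants" and "The group without left ventricular assist device insertion: more than 600 participants".

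**Power.** Section 9.3 (2) states: "With the above number of patients, it has about 88% statistical power to detect an odds ratio of 1.56". The planning rates are "odds ratio of 1.56 (inserted group = 0.3, non-inserted group = 0.4". Power is put at 84% after 10% dropout and above 90% for a one-sided test. The section then predicts that the plan will succeed both statistically and clinically. The method cited is Fleiss, Tytun and Ury.

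**Planned test.** Section 15.3 describes one comparison of in-hospital death by device use. It is made "using chi-square tests among those who receive a certain level of vasoactive drugs". Neither the drug level nor the number of patients expected to reach it is given.

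**Eligibility.** The blood-pressure criterion in section 9.1 can be met by hypotension alone. The alternative is "or Use of pressure boosting agents is necessary".

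**Expected deaths.** Section 15.3 justifies the prediction model "with an expected mortality rate of about 40%, or approximately 400 deaths", at 10 to 15 events per variable.

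**The concern.** The power statement and the test it appears to support refer to different sets of patients. Section 9.3 counts the whole cohort. Section 15.3 uses only those above a vasoactive-drug level, and entry does not require vasoactive drugs at all. Nothing in the protocol makes the two sets equal. With the same rates, removing patients from either group lowers power, so a reader who carries the 88% over to the chi-square test in section 15.3 is relying on a figure computed for something else. Section 9.3 does rely on it, because its forecast of success follows directly from these numbers.

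A second, smaller mismatch lies in the planning rates. Group rates of 30% and 40% cannot average to 40% overall, yet section 15.3 uses 40% overall to count events.

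**Working it through.** **Inputs.** n1 = 400 (device) and n2 = 600 (no device), from section 9.3 (1). p1 = 0.30 and p2 = 0.40, from section 9.3 (2); they are read as death rates because that section treats the device group as the superior one. Alpha is not stated, so 0.05 two-sided is assumed.

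**Formula** (normal approximation with continuity correction):

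- pooled rate p = (n1·p1 + n2·p2)/(n1 + n2)
- SE0 = √[p(1−p)(1/n1 + 1/n2)]
- SE1 = √[p1(1−p1)/n1 + p2(1−p2)/n2]
- c = ½(1/n1 + 1/n2)
- power = Φ{(|p1−p2| − c − z·SE0)/SE1}, with z = 1.960 two-sided or 1.645 one-sided

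**Step 1: reproduce the stated figures.**

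- Odds ratio: (0.4/0.6)/(0.3/0.7) = 1.556, stated as 1.56.
- 400 vs 600: p = 0.36, SE0 = 0.03098, SE1 = 0.03041, c = 0.00208. (0.1 − 0.00208 − 1.960 × 0.03098)/0.03041 = 1.22, so power is 88.9% (stated 88%). Without the correction it is 90.2%.
- After 10% dropout, 360 vs 540: 85.3% (stated 84%).
- One-sided 0.05: 93.9% at 1,000 and 91.5% at 900 (stated above 90%).

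All three agree to within about two points when the full group sizes are used. The arithmetic in section 9.3 is sound for its own inputs.

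**Step 2: power in a subset.** The subset size is not in the documents, so these are scenarios. Rates stay at 30% vs 40%, two-sided 5%, continuity-corrected, before dropout.

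| Device | No device | What is removed | Power |
|---|---|---|---|
| 400 | 600 | nothing | 88.9% |
| 400 | 480 | 20% of controls | 86% |
| 400 | 420 | 30% of controls | 83% |
| 400 | 360 | 40% of controls | 80% |
| 400 | 300 | 50% of controls | 76% |
| 320 | 480 | 20% of both | 81% |
| 280 | 420 | 30% of both | 75% |
| 240 | 360 | 40% of both | 68% |
| 200 | 300 | 50% of both | 59% |

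A subset keeping 95% of both groups would still have about 87%. With equal removal from both groups, power falls below 80% once less than about 79% of the cohort remains.

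**Step 3: expected deaths.**

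- 0.30 × 400 + 0.40 × 600 = 120 + 240 = 360, and 360/1,000 = 36%. Section 15.3 has 400 and 40%.
- If the non-device group is at 40% and the cohort is at 40%, the device group must also be at 40%. That would leave no device effect.
- Predictors supported by 360 deaths: 360/15 = 24 to 360/10 = 36. By 400 deaths: 400/15 = 26.7 to 400/10 = 40.

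**The case against.** The strongest reply is that the loss may be small.

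- **Subset size.** Section 9.1 shows that vasoactive drugs are not required for entry. It does not show that many patients go without them.
- **Who is removed.** Sections 6.2 and 11.2 describe devices as generally used once drugs have failed, with operator discretion as the exception. The restriction would then remove mainly non-device patients, and even halving that group leaves about 76%.
- **Other unknowns.** The group sizes are minima, so over-enrolment could recover some power. Death rates in a sicker subset may not be 30% and 40%.

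All of this stands. A reader might infer that the planned test is badly underpowered, for example at 59%. The documents do not support that: 59% needs half of both groups to be lost, and nothing says so.

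A reader might also treat the unset drug level as a fault in itself. A threshold is commonly left to a SAP, which is not at hand. The fault is only that a whole-cohort power is attached to a plan whose device test is restricted, and fixing the threshold later would not by itself correct the figure.

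Nor does it follow that the restriction should be dropped in favour of a whole-cohort comparison adjusted for vasoactive dose. The restriction may make severity more alike, and section 9.3 itself warns that the groups are not comparable. Section 11.1 records the maximum dose, which may be reached after insertion. An adjusted model would not have the stated 88% either.

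On deaths, the protocol words both 40% and 400 as approximate, and 36% depends on reading 0.3 and 0.4 as death rates. A shortage of events does not follow.

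Finally, this is a registry in which section 15.3 puts the prediction model first and adds the device comparison after it. That limits the consequence. It does not make the power statement apply to the test.

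**Conclusion.** The point holds in limited form. The 88%, 84% and over-90% figures are correct for 400 vs 600 patients, but they do not describe the device comparison planned in section 15.3. That comparison's power cannot be determined from the protocol. Under the scenarios shown it runs from about 86% down to 76% if only controls are lost (480 to 300 remaining), and from about 81% down to 59% if both groups shrink to between 80% and 50%. These values assume a two-sided alpha of 0.05, unchanged rates of 30% and 40%, exactly the minimum group sizes before restriction, and no dropout. The forecast of success in section 9.3 is unsupported so far as it rests on the whole-cohort figure.

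The mismatch of 360 against 400 deaths is real but secondary. It is a 10% difference, and the conclusion that there are enough events is unaffected.

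**What to change.** 1. In section 9.3, label 88%, 84% and over 90% as whole-cohort figures, and state the alpha.
2. State the expected size of the vasoactive-drug subset, separately for device and non-device patients, and restate the power for it. If the size cannot be predicted, give a range such as the one above.
3. Withdraw the prediction of statistical and clinical success to the extent that it rests on the whole-cohort power.
4. If the 88% is meant to describe a planned analysis, a whole-cohort chi-square test may be reported alongside the restricted one.
5. Restate the expected deaths in section 15.3 as about 360 (24 to 36 predictors at 10 to 15 events each), or change the group rates in section 9.3 so that the two sections agree.

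The cost is a few sentences and a short recalculation. No extra patients or data are needed. The power quoted for the device comparison will be lower than 88% unless the restriction removes almost nobody or enrolment exceeds the minima.

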Recently, in a study conducted by Thiele et al., the superiority of IABP treatment was not demonstrated compared to standard treatment group in patients with cardiogenic shock accompanied by acute myocardial infarction for whom early coronary intervention was scheduled [2]. As a result, research on the effectiveness and safety of mechanical circulatory support devices that can more effectively assist left ventricular function in cardiogenic shock is being actively pursued worldwide [3-6]. In particular, the expected benefits of ECMO, a left ventricular assist device that can be operated anywhere in emergency situations, are significant, and interest in ECMO procedures is rapidly increasing in Korea, with the number of procedures increasing rapidly. Therefore, it is urgent to evaluate the appropriateness and effectiveness of ECMO and conduct research on its effects.

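### The power figure above 90% rests on a one-sided test justified by presuming device superiority, and it does not describe the comparison planned in section 15.3

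*Protocol*

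**What the plan says.** Protocol section 9.3 sets two group targets: "The group with left ventricular assist device insertion: more than 400 participants" and "The group without left ventricular assist device insertion: more than 600 participants". Its background text then gives three power statements.

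- Full numbers: "With the above number of patients, it has about 88% statistical power" "to detect an odds ratio of 1.56 (inserted group = 0.3, non-inserted group = 0.4".
- After losses: "if an expected dropout rate of about 10% is taken into account, the power is reduced to 84" per cent.
- One-sided: "considering that the group with LVADs inserted is significantly superior to the group without LVADs, a one-sided test is usually performed". With that adjustment the power is said to exceed 90%, and the section concludes that the plan should succeed both statistically and clinically.

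The method cited is Fleiss, Tytun and Ury (1980). No significance level is given anywhere in the protocol.

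Four other places bear on the premise of superiority:

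- Section 6.1 makes determining the treatment effects of IABP and ECMO an aim of the study.
- Section 6.2 says that large systematic Korean studies of these effects are lacking. It also reports a randomised trial in which "the superiority of IABP treatment was not demonstrated compared to standard treatment group".
- The paragraph of 9.3 before the one-sided argument says of device patients that "most of them are critically ill patients", and warns that the two groups cannot be compared on equal terms.
- Section 15.3 plans chi-square tests of in-hospital death with and without a device, among patients receiving a certain level of vasoactive drugs. It states no direction.

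**The concern.** The reason given for a one-sided test is the conclusion that the comparison is meant to examine. Expecting benefit is not enough to justify one-sidedness when the opposite result is plausible and would matter. Here it is plausible: section 11.2 says devices are typically inserted when drugs have failed, so crude mortality may well be higher in the device group through severity alone.

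Two things are at stake. First, the reader is given a power above 90% that does not belong to the test named in section 15.3. Second, with no alpha stated and no direction fixed in 15.3, section 9.3 is the only text on sidedness, and it favours one-sided testing. It could be cited after the data are seen to report a benefit with a two-sided p-value between 0.05 and 0.10 as significant.

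**Working it through.** **Inputs.** From section 9.3: n₁ = 400 with a device and n₂ = 600 without, so k = n₂/n₁ = 1.5; p₁ = 0.30 and p₂ = 0.40, so d = 0.10; dropout 10%, giving 360 and 540. Alpha is assumed to be 0.05.

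**Odds ratio.** (0.4/0.6)/(0.3/0.7) = 1.556, which matches the stated 1.56.

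**Formula.** The continuity correction is applied by reducing n₁ to an effective size

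n = (n₁ − c/4)²/n₁, with c = 2(1 + 1/k)/d = 2 × 1.6667/0.10 = 33.33, so c/4 = 8.33.

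Power = Φ[(d√n − z·s₀)/s₁], where

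- p̄ = (0.30 + 1.5 × 0.40)/2.5 = 0.36
- s₀ = √(0.36 × 0.64 × 1.6667) = 0.6197
- s₁ = √(0.30 × 0.70 + 0.40 × 0.60/1.5) = 0.6083

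**Effective sizes.** At 400/600, n = 391.67²/400 = 383.5 and d√n = 1.9583. At 360/540, n = 351.67²/360 = 343.5 and d√n = 1.8534.

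**The protocol's own figures (two-sided, z = 1.960, z·s₀ = 1.2145).**

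- 400/600: (1.9583 − 1.2145)/0.6083 = 1.223, power 88.9% (stated: about 88%).
- 360/540: (1.8534 − 1.2145)/0.6083 = 1.050, power 85.3% (stated: 84%).

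Both agree within about 1.3 points, so two-sided 5% is a reasonable reading of the first two statements.

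**One-sided 5% (z = 1.645, z·s₀ = 1.0193).**

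- 400/600: (1.9583 − 1.0193)/0.6083 = 1.544, power 93.9%.
- 360/540: (1.8534 − 1.0193)/0.6083 = 1.371, power 91.5%.

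Both are consistent with the claim of more than 90%.

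| | Two-sided 5% | One-sided 5% | One-sided 2.5% |
|---|---|---|---|
| 400/600 | 88.9% | 93.9% | 88.9% |
| 360/540 | 85.3% | 91.5% | 85.3% |

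The gain is 5.0 points at full numbers and 6.2 points after dropout. It vanishes when the one-sided test is held at 2.5%, so all of it comes from lowering z from 1.960 to 1.645.

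**Sensitivity to the correction.** Without the continuity correction, two-sided power is 90.2% at 400/600 and 86.9% at 360/540. The full-cohort figure can thus just pass 90% two-sided under a method other than the one cited. After dropout it cannot under either.

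**If a one-sided benefit test were actually run.** Suppose the device group truly had the higher mortality, 0.40 against 0.30. The one-sided test would reject in favour of devices with probability about 5 × 10⁻⁷, and by construction it could not declare excess mortality. A two-sided test would show the excess with about 89% power at 400/600 and about 86% at 360/540 (continuity-corrected).

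**The case against.** Several points on the other side have force.

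- **The one-sided test is never adopted as the analysis.** It appears only as a closing remark on power, and section 15.3 does not take it up. This stands. A reader might infer that the plan makes harm undetectable or doubles the false-benefit rate. The documents do not support that as a flat statement; both consequences follow only if the one-sided test is used. If it is not used, the fault is a power figure for a test that is not planned.
- **Section 15.3 does not say its chi-square test is two-sided.** Correct. That it is non-directional is the usual form of the test, not protocol text.
- **No alpha is stated.** Correct. The 5% level is an assumption, supported by the near match to 88% and 84%.
- **The background does not refute superiority.** A reader might infer that the protocol contradicts itself outright, but it does not. The cited trial concerned IABP in infarction patients scheduled for early coronary intervention, whereas the device group here includes ECMO and other causes of shock. Section 6.2 also speaks of significant expected benefits from ECMO. The remark about critically ill patients concerns comparability, not the direction of the treatment effect. Superiority is left unsupported, not disproved.
- **Nothing in the design depends on the remark.** This also stands. The feasibility estimate behind 1,000 patients is about 200 a year over five years, and two-sided power is already about 88%, or 84% after dropout. The device comparison is also listed after the logistic regression for predictors of death.

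These points limit the consequence. They do not rescue the justification, which remains circular, or the figure it produces.

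**Conclusion.** The point holds in a limited form, and the text should be fixed. Section 9.3 raises the stated power above 90% by presuming the result under study. Under an assumed alpha of 0.05 and the cited method, the step is worth 5 to 6 percentage points and comes entirely from the relaxed critical value. After 10% dropout, two-sided power does not reach 90% with or without the continuity correction. Taking the chi-square test of section 15.3 in its usual form, the higher figure does not describe the planned comparison.

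The consequences for error rates and for detecting harm are conditional on a one-sided benefit test actually being used, which the protocol does not establish. The enrolment target is unaffected.

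**What to change.** - In section 9.3, delete the paragraph that argues for a one-sided test, including the figure above 90% and the conclusion that the plan will be successful.
- In sections 9.3 and 15.3, state that the device comparison is two-sided at the 5% level.
- Quote only the two-sided power, about 88% and 84% after 10% dropout. Label it as applying to the full 400/600 cohort. It does not describe the comparison in section 15.3, which is limited to patients on a certain level of vasoactive drugs, a subset whose size is not given.

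The cost is a text edit and a slightly less favourable stated power. The target of 1,000 and the endpoints do not change.

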### Referene:

\*The above power calculation was generated using nQuery Advisor 4.0.

## **10. Duration of clinical trial**

IRB approval date ~ December 31, 2019 (registration period: IRB approval date ~ December 31, 2018).

Data collection period: January 1, 2014 ~ December 31, 2019 (6 years).

## **11. Clinical trial method**

### **11.1. Overview**

Shock patients with cardiogenic shock caused by acute myocardial infarction, myocardial disease, myocarditis, etc. will be registered both retrospectively and prospectively for two and a half years before and after IRB approval. Patients undergoing coronary intervention and treatment are performed according to the standard method recommended by the Korean Society of Cardiology. If the patient satisfies the above conditions and meets other inclusion and exclusion criteria, we obtain the patient's consent and enroll them in the study. On the day of shock occurrence, we perform physical measurements, blood tests, investigate the medication being taken, and record the most severe signs of vitality on that day. The maximum dose of medication used for shock treatment, the insertion of a left ventricular assist device, and indicators of shock deterioration and improvement are followed up. We conduct tests scheduled for the day of shock occurrence and one month, six months, and twelve months afterward to confirm whether a death event occurred. If the subject is unable to visit the hospital due to unavoidable circumstances, the trial responsible person or the person delegated by the trial responsible person may follow-up and check the subject's survival status and death event by phone.

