| Duration                       | IRB approval date ~ December 31, 2019 (registration period: IRB approval date ~ December 31, 2018).
Data collection period: January 1, 2014 ~ December 31, 2019 (6 years).                                                                                                                                                                                                                                                                                                                                                                                                                                                                                                                                                                                                                                                                                                                                                                                                                                                                                                                                                       |
| Design                         | Retrospective and prospective, open, multi-center, and observational registry study                                                                                                                                                                                                                                                                                                                                                                                                                                                                                                                                                                                                                                                                                                                                                                                                                                                                                                                                                                                                                                                 |

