## 12. Observation items/clinical examination items and observation/testing methods

### 12.1. Visit 1 (day of shock occurrence)

#### ① Written informed consent for patients enrolled

According to the scope of data collection, it is divided into prospective data collection subjects and retrospective data collection subjects.

- Prospective data collection subjects: The day of shock occurrence is after the IRB approval date
- Retrospective data collection subjects: The day of shock occurrence is before the IRB approval date

For prospective data collection subjects, before entering the clinical trial, the purpose and content of the trial should be explained in detail to the subject or legal guardian (in the case of a subject who cannot provide consent for the trial), and the written consent form should accurately record the signature dates of the subject and investigator. The original signed consent form is kept by the subject, and a copy is provided to the subject. If the subject is unable to consent on the day of the shock occurrence, the consent form is obtained from the representative of the accompanying subject. In this case, the principal investigator and sub-investigator must inform the subject or the subject's representative about the clinical trial as soon as possible and obtain consent to continue participating in the trial. If the subject recovers to a condition where consent can be given, the consent form is obtained from the subject.

For retrospective data collection subjects, only data corresponding to the study protocol are collected until IRB approval is obtained without written consent. However, among shock occurrence subjects before IRB approval, those who have obtained written consent are eligible for both prospective and retrospective data collection.

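### The device comparison in 15.3 pools the retrospective and prospective cohorts in one unstratified chi-square test, so cohort differences can bias it in either direction

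*Protocol*

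**What the plan says.** The Summary describes the design as "Retrospective and prospective, open, multi-center, and observational registry study". Under 11.1, patients "will be registered both retrospectively and prospectively for two and a half years before and after IRB approval". Section 10 gives the outer dates: "Data collection period: January 1, 2014 ~ December 31, 2019 (6 years"), with "registration period: IRB approval date ~ December 31, 2018".

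Section 12.1, item 1, defines the two cohorts by shock date: "Prospective data collection subjects: The day of shock occurrence is after the IRB approval date" and "Retrospective data collection subjects: The day of shock occurrence is before the IRB approval date". Prospective subjects need consent from themselves or a representative. Retrospective data are collected without written consent, although some pre-approval patients may have given it and then belong to both parts.

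Section 15.3 fixes the device comparison: "we plan to compare the in-hospital death rate between patients with and without left ventricular assist devices using chi-square tests". It restricts this to patients on an unspecified level of vasoactive drugs. It does not limit the test to one cohort and does not stratify by cohort or calendar period. Section 6.2 remarks that "interest in ECMO procedures is rapidly increasing in Korea, with the number of procedures increasing rapidly". Section 9.3 concedes that the device groups are not comparable, but the reason it gives is severity of illness, not period or mode of registration.

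**The concern.** The two cohorts differ in calendar period (a span of about five years) and in how patients enter. A single two-by-two chi-square ignores this. If the share of patients given a device differs between cohorts, and so does mortality, part of the between-cohort difference in mortality is read as a device effect. Adjusting for severity, the one imbalance that 9.3 acknowledges, would not necessarily remove it.

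At stake are the estimate and the type I error of the only comparison the protocol fixes for the effect of devices on in-hospital death. A separate SAP may exist, but this is not a detail left open: 15.3 already names the test.

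**Working it through.** **The plan's own figure.** Section 9.3 states about 88% power for 0.30 versus 0.40 with 400 and 600 patients, and 84% after 10% dropout. Alpha is not stated; I assume two-sided 0.05. With the Fleiss-Tytun-Ury correction, the effective device-group size is n1 − (r+1)/(r·d) = 400 − 2.5/(1.5 × 0.10) = 383.3, which gives 88.9%. At 360 versus 540 the result is 85.3%. Without the correction the figures are 90.2% and 86.9%. The stated power is reproduced to within 2 points and is not in dispute.

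**Inputs for the cohort effect.** From the protocol: 400 device and 600 no-device patients (9.3), overall mortality about 40% (15.3), and a planned difference of 10 points (9.3). Assumed, because the protocol does not give them: 500 patients per cohort (11.1 divides time, not patients), device use by cohort, mortality by cohort, and no true device effect.

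**Formula.** With no device effect, the pooled difference is (m1 − m2) × (a − b). Here m1 and m2 are the retrospective and prospective mortalities, a is the fraction of device patients who are retrospective, and b is the same fraction of no-device patients. For device use of 30% then 50%: a = 150/400 = 0.375, b = 350/600 = 0.583, and 10 points × (−0.208) = −2.08 points. The type I error is the normal-approximation rejection probability of the two-sided 5% test at these pooled rates.

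| Device use, retro → prosp | Mortality, retro → prosp | Device | No device | Difference (points) | Odds ratio | Type I error |
|---|---|---|---|---|---|---|
| 40% → 40% | 45% → 35% | 160/400 = 40.00% | 240/600 = 40.00% | 0 | 1.00 | 5.0% |
| 35% → 45% | 45% → 35% | 157.5/400 = 39.38% | 242.5/600 = 40.42% | −1.04 | 0.96 | 6.2% |
| 30% → 50% | 45% → 35% | 155/400 = 38.75% | 245/600 = 40.83% | −2.08 | 0.92 | 10.1% |
| 20% → 60% | 45% → 35% | 150/400 = 37.50% | 250/600 = 41.67% | −4.17 | 0.84 | 26.0% |
| 30% → 50% | 35% → 45% | 165/400 = 41.25% | 235/600 = 39.17% | +2.08 | 1.09 | 10.1% |

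The last row shows the sign reversing when mortality rises. A smaller mortality gap (42.5% to 37.5%) with use of 30% to 50% gives −1.04 points and 6.2%. A larger gap (47.5% to 32.5%) with use of 20% to 60% gives −6.25 points and 50.7%.

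The difference in points does not depend on the total sample size, but the type I error does. The restriction to patients on vasoactive drugs would make the tested set smaller and the inflation milder.

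**Power after stratifying by cohort.** Cochran-Mantel-Haenszel, 0.30 versus 0.40 in each cohort, no continuity correction, stratum weight w = n1·n2/500. For 20% to 60% use, the weights are 100 × 400/500 = 80 and 300 × 200/500 = 120. Then z = 0.10 × 200 / √(80 × 0.38 × 0.62 + 120 × 0.34 × 0.66) = 20/6.77 = 2.96, and power is 84.0%. The same steps give 88.5% for 30% to 50%, 89.5% for 35% to 45%, and 89.8% for equal use, against 90.2% unstratified. The gap at equal use reflects the variance formula, not a cost of stratifying.

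**The case against.** A reader might infer more: that because ECMO is rising, device patients cluster in the later cohort, no-device patients act as historical controls, and the bias runs towards benefit. The protocol does not support this.

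- **Device use.** Section 6.2 reports a rising number of ECMO procedures in Korea. It does not give the share of shock patients treated or anything about these sites. The exposure in 15.3 combines IABP and ECMO, and 6.2 also notes that a randomised trial did not show IABP to be superior. The combined share could be flat, and then the bias is zero.
- **Mortality.** No section gives mortality over time. Section 6.2 says that about 40% is still reported despite newer treatments.
- **Capture.** Early deaths missed for lack of consent could push either way. Patients who die before consent may also die before a device can be inserted. As an illustration, assume 45% mortality throughout, use of 30% to 50%, and 25 prospective no-device deaths missed. The device group shows 180/400 = 45.0% and the no-device group 245/575 = 42.6%, so the device looks worse. Consent by a representative, allowed in 12.1, limits such losses.
- **Consent rules.** Inclusion criterion 5, section 11.1 and note 1 of the flow chart ask for consent without exempting retrospective cases, while 12.1 waives it. Until these are reconciled, it is not settled which cohort is more likely to lose deaths.

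All of this stands against a claim of certain or directional bias. None of it answers the narrower point: a pooled chi-square cannot account for cohort, and the data needed to do so are already collected.

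**Conclusion.** The point holds as a risk of confounding by cohort, of unknown size and direction. It needs both device use and mortality to differ between cohorts; if either is constant, this bias is zero. Under the assumed inputs with mortality of 45% then 35%, the spurious difference runs from 0 to about 4 points of the planned 10, and the two-sided type I error from 5% to about 26%. Moderate shifts in use give 1 to 2 points and 6% to 10%. That would not produce the planned effect by itself, but it is enough to make the nominal 5% level unreliable. Because the protocol cannot say where in this range the registry will fall, the analysis should not depend on the answer.

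**What to change.** In 15.3, replace the pooled chi-square with a comparison stratified by cohort (shock before or after the site's IRB approval date), for example Cochran-Mantel-Haenszel. Calendar period could serve as the stratum instead. The two largely coincide, separating only around each site's approval date, so both are not needed. Report device use and in-hospital death within each cohort beside the stratified estimate.

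State in the text what this does not correct: confounding by severity, and selective loss of early deaths within the prospective cohort. In the illustration above with 25 missed deaths, the prospective stratum would still show 45.0% versus 87.5/225 = 38.9%.

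The cost is a wording change and no new data, since the shock date already defines the cohorts. Power falls from about 90% to between 88.5% and 90% for equal or moderately shifting device use, and to 84% for a shift from 20% to 60%. Adding cohort or period to the general prognostic logistic model is optional and can be left to the SAP.
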